### Measures

Participants completed three online surveys (baseline, post-intervention at 5 months and 12-month follow-up) via QuestionPro, a secure online survey platform licensed by the University of Newcastle. The baseline survey was completed after all participants were enrolled and prior to their first therapy session. The post-intervention survey was completed approximately 1 week after their last therapy session (which was at 5 months post baseline), and the follow-up survey will be completed at 12 months post baseline. Participants will receive an email containing a personalised survey link at each time point. To promote retention and maximise completions at post-study and follow-up, participants who have not responded within 1 week will receive a reminder email, followed by a reminder telephone call and text message if needed. Participants who remain unresponsive will be sent an abbreviated survey containing the primary outcome measure only (DASS-21), consistent with an intention-to-treat approach. At the end of each week, survey data will be exported from QuestionPro and imported into a password-protected database stored on a secure University of Newcastle OneDrive server. All identifying information will be replaced with a unique numerical participant code prior to analysis; however, a separate password-protected linkage file will be retained by the research team to enable longitudinal data linkage across time points. Only members of the research team will have access to identifiable data.

#### Primary outcome

##### Psychological distress

Overall psychological distress was assessed using the composite score of the DASS-21 measure.^41^ The DASS-21 is a widely used and extensively validated measure of commonly experienced symptoms associated with depression, anxiety and stress over the previous week. Participants rated each item on a 4-point scale ranging from 0 (did not apply to me) to 3 (applied to me very much). To allow for comparison with the original DASS-42 scale, total scores were calculated and then doubled as recommended, with higher scores indicating worse mental health.

Although men with depressive symptoms are the target sample, the primary outcome was informed by pilot trial data, which showed comparable reductions in depressive symptoms across conditions but a potential signal favouring walk-and-talk therapy on overall psychological distress. Given anxiety and stress commonly co-occur with depression,^42^ the current trial was designed to provide an adequately powered test of this preliminary effect on overall distress, which also has a theoretical basis given the established links between physical activity,^43^ nature exposure^44^ and symptoms of depression, anxiety and stress.^45
46^

### Survey measures

Survey measures including secondary outcomes and other measures are outlined in table 1. Other measures included treatment expectancies and preferences, and therapeutic process indicators.

**Table 1 T1:** Survey measures

Outcome	Measure	Reference	Items	Example item	Anchors	Base-line	5-month	12-month
Primary outcome								
Overall psychological distress	Depression, Anxiety and Stress Scale (DASS-21)	^ 41 ^	21	See below	4-point scale: Did not apply to me (0) to applied to me very much (3)	X	X	X
Secondary outcomes								
Depression	Depression subscale (DASS-21)	^ 41 ^	7	I couldn't seem to experience any positive feeling at all	4-point scale: Did not apply to me (0) to applied to me very much (3)	X	X	X
Anxiety	Anxiety subscale (DASS-21)	^ 41 ^	7	I was aware of dryness of my mouth	4-point scale: Did not apply to me (0) to applied to me very much (3)	X	X	X
Stress	Stress subscale (DASS-21)	^ 41 ^	7	I found it hard to wind down	4-point scale: Did not apply to me (0) to applied to me very much (3)	X	X	X
Male-type depression symptoms	Male Depression Risk Scale (MDRS-7)	^ 54 ^	7	I overreacted to situations with aggressive behaviour	5-point scale: None of the time (0) to all the time (4)	X	X	X
Mental well-being	Warwick-Edinburgh Mental Well-being Scale – Short Version (SWEMWBS)	^ 55 ^	7	I’ve been thinking clearly	5-point scale: None of the time (1) to all the time (5)	X	X	X
Suicidal ideation	Suicidal Ideation Attributes Scale (SIDAS)	^ 56 ^	5	In the past month, how often have you had thoughts about suicide?	10-point scale: Anchors vary by item	X	X	X
Quality of life	Short Form-12 survey (SF-12)	^ 57 ^	12	In general, would you say your health is:	Varied	X	X	X
Physical activity	International Physical Activity Questionnaire (IPAQ) Short Form	^ 58 ^	6	During the last 7 days, on how many days did you walk for at least 10 min at a time?	Open response	X	X	
Sleep quality	Brief Version of the Pittsburgh Sleep Quality Index (B-PSQI)	^ 59 ^	6	During the past month, when have you usually gone to bed at night?	Varied	X	X	
Mental restoration	Restoration Outcome Scale (ROS-6)	^ 60 ^	6	When I was participating in my therapy sessions, my concentration and alertness clearly increased	7-point scale: Not at all (1) to totally (7)		X	
Engagement in valued activities	Behavioural Activation for Depression Scale Short Form (BADS-SF)	^ 61 ^	9	I was an active person and accomplished the goals I set out to do	8-point scale: Not at all (0) to completely (7)	X	X	
Emotional control	Conformity to Masculine Norms-46 (CMNI-46): Emotional Control subscale	^ 62 ^	6	I hate it when people ask me to talk about my feelings	4-point scale: Strongly disagree (1) to strongly agree (4)	X		
Nature connection	Connection with Nature Instrument (CN-12)	^ 63 ^	12	I feel right at home when I am in nature	7-point scale: Strongly disagree (1) to strongly agree (7)	X	X	
Nature contact	Nature Contact	^ 64 ^	1	Over the past month, approximately how many hours per week on average would you consider yourself to have interacted with nature? For example, walking outside, biking, gardening, playing games/sports, camping, fishing, reading outside, yard work, hanging out in a park, etc	Open response	X	X	
Other measures								
Therapy expectancies and preferences	Treatment Acceptability Preferences Scale (TAPS): Expectancies	^ 65 ^	8	How effective do you think this approach would be for improving your mood?	5-point scale: Not at all (0) to very much (4)	X		
	Treatment Acceptability Preferences Scale (TAPS): Preference		1	Do you have a preference for one of the two approaches to therapy?	No; yes - outdoor walk-and-talk; yes - conventional indoor	X		
Therapeutic process indicators	Individual Therapy Process Questionnaire (ITPQ): Global Alliance and Patient Fear subscales	^ 66 ^	5	Today, I felt comfortable in the relationship with the therapist (Global Alliance) Today, it was difficult for me to talk openly with the therapist (Patient Fear)	5-point scale: Does not apply (0) to fully applies (4)	*		

* Measure completed via texted survey after participants’ first, middle and final session.

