#### Interventions

In both conditions, participants were invited to attend 10 fortnightly 60-minute individual psychotherapy sessions over 20 weeks. Participants were scheduled to attend one session per fortnight on the same day and time, with the same psychologist and within their allocated condition. If a participant missed a session, they were offered the opportunity to reschedule with the same psychologist within a time slot allocated to their assigned treatment condition, pending psychologist availability. There was no cost to participants for the sessions.

The sessions were delivered by provisionally registered (n=1) or registered (n=12) psychologists. The provisional psychologist received weekly supervision from a senior registered clinical psychologist during the trial. To prevent confounding, all psychologists delivered therapy in both study arms. Members of the research team delivered a half-day training session for the psychologists prior to working with participants, which involved walking the therapy route, contingency planning, strategies for maintaining safety and confidentiality and details on the proposed therapy style.

The sessions involved a non‐directive supportive therapy style using counselling micro‐skills to address important issues identified by the participant.^39^ This approach remained consistent in each study arm and was selected for the current study for several reasons: (1) it could be feasibly delivered in both indoor and outdoor environments (compared with other approaches which require access to worksheets, manuals or other resources), (2) it maintained the focus of the trial on the experimental manipulation (ie, the conventional indoor vs walk-and-talk context), (3) all psychologists in Australia are required to demonstrate competency with this approach during their training and (4) it is effective for treating depression.^39
40^

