Depending on which group they were randomised to, participants received therapy in a conventional indoor seated environment (usual care) or an outdoor, walking environment (walk-and-talk) for the duration of the study. In the conventional indoor therapy arm, sessions occurred in private consultation rooms in the Behavioural Sciences (W) Building at the University of Newcastle Callaghan Campus. The space included two sound-proofed consultation rooms, a research office and a private waiting area. The consultation rooms each contained a bookshelf, two large therapy chairs, a coffee table and a window (approximately 1 m × 2 m) with a view of surrounding campus infrastructure (ie, paved walkways and buildings), with some greenery visible (ie, monstera plants and lawn). In contrast, the walk-and-talk therapy sessions began outside the office and then occurred while walking along an approximately 4 km predetermined route on the University campus. Psychologists were advised to follow the same walking route with participants for each session, but were permitted to make minor variations (eg, extending or shortening the route, or sitting at an outdoor bench for part of the session) based on participant capacity and environmental conditions (eg, heat or heavy rain). To minimise any physical risks, the route followed well-maintained walking paths on campus, including both built elements (eg, paved footpaths and near buildings) and non-built elements (ie, a 20-minute bushwalk component in a biodiverse nature reserve through the university wetlands) (see online supplemental figures 1 and 2). Participants in the walk-and-talk group were provided with umbrellas, sunscreen, and/or insect repellent, as needed, to maintain physical safety standards during the sessions.

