Strengths of this study protocol include a randomised design with an active intervention control group (conventional indoor therapy), a preregistered, detailed statistical analysis plan that will follow the intention-to-treat principle and the inclusion of a 12-month follow-up to measure the longer-term treatment outcomes. In addition to measuring overall psychological distress (depression, anxiety and stress), a comprehensive range of secondary outcomes will also be assessed to capture other psychological (male-type depression symptoms, mental well-being, suicidal ideation, quality of life), behavioural (physical activity, sleep, nature contact), social (nature connection, emotional control, engagement in valued activities, mental restoration) and economic (costs) impacts of the programme. By successfully completing this trial, insights into the efficacy of an innovative psychotherapy approach for men will be generated through various analytical methods (eg, mediation and moderation analyses). Lastly, recruitment efforts will focus on men residing in areas identified as socio-economically disadvantaged to ensure a diverse sample. Limitations of the current study include reliance on psychologist self-report to assess adherence to the therapy modality, as sessions are not independently coded. This approach was necessary due to the practical challenges of recording sessions in outdoor settings; however, it may introduce bias into the fidelity assessment. Furthermore, data relating to therapist favourability to a particular therapy setting were not collected, which may represent an additional source of bias; future trials building on this work would benefit from collecting therapist allegiance data to enable assessment of its potential influence in sensitivity analyses. The power calculation did not account for therapist-level clustering; the extent to which this affects statistical power will depend on the magnitude of the therapist-level intraclass correlation coefficient, which will be reported alongside the trial outcomes. In addition, participants self-select into a trial conducted at a university campus, which may limit generalisability to other clinical populations and health service settings. Individuals who are willing to participate in such trials may be more motivated or more receptive to novel therapeutic approaches than the general population. As such, further research will be needed to evaluate this intervention when implemented within routine care contexts.

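### The 5-month Nature Contact item can include the walk-and-talk sessions themselves, so a group difference on it cannot by itself be read as behaviour change outside therapy

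*Protocol article*

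**What the plan says.** Table 1 of the protocol article (Survey measures) lists nature contact as a secondary outcome, read at baseline and 5 months but not at 12 months. It is a single open-response item that begins "Over the past month, approximately how many hours per week on average would you consider yourself to have interacted with nature? For example, walking outside" and goes on to other outdoor pursuits such as gardening and camping.

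On timing, the Measures section states "The baseline survey was completed after all participants were enrolled and prior to their first therapy session" and "The post-intervention survey was completed approximately 1 week after their last therapy session". On dose, the Interventions section states that "participants were invited to attend 10 fortnightly 60-minute individual psychotherapy sessions over 20 weeks".

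The same section sets out the contrast between arms. Walk-and-talk sessions "occurred while walking along an approximately 4 km predetermined route on the University campus", which includes "a 20-minute bushwalk component in a biodiverse nature reserve through the university wetlands". In the comparator arm, "sessions occurred in private consultation rooms in the Behavioural Sciences (W) Building".

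The Primary analysis plan tests secondary outcomes by the group-by-time term of a linear mixed model and treats p<0.05 as suggestive only. The Discussion lists the outcome among the programme's impacts under the label "behavioural (physical activity, sleep, nature contact".

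**The concern.** At baseline the item measures daily life in both arms. At 5 months, for a man who kept to the schedule, it can measure daily life plus delivered treatment in the walk-and-talk arm, and daily life alone in the indoor arm. A man who attended his walks and changed nothing else could truthfully report more hours. Session time can only push the group-by-time estimate in favour of walk-and-talk.

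The article groups this outcome with physical activity and sleep as behavioural. Many readers will take that to mean that men went outdoors more in their own time. The 5-month score cannot separate that from the treatment itself, and no later reading of the item is planned that would fall clear of the sessions.

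**Working it through.** **The plan's own figure.** The article gives no expected value, SD or power for nature contact. Its only sample-size figure is for the DASS-21: difference 8, SD of change 15, alpha 0.05 (taken as two-sided), power 80%. This reproduces: 2 × (1.960 + 0.842)² × (15/8)² = 55.2, rounded up to 56 per group; 56/0.75 = 74.7, rounded up to 75. The 56 is borrowed below only as a plausible number of responders.

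**Sessions inside the recall month.** With the survey 7 days after session 10 and sessions 14 days apart:

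- session 10: 7 days before the survey, inside
- session 9: 7 + 14 = 21 days before, inside
- session 8: 21 + 14 = 35 days before, outside

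Two sessions therefore count.

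**Hours per week added in the walk-and-talk arm.** Formula: sessions × hours per session ÷ weeks in the window. A month of 30.4 days is 30.4/7 = 4.34 weeks.

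- Whole hour counted: 2 × 1 / 4.34 = 0.46 h/week (0.50 for a 28-day window, 0.45 for 31 days).
- Only the bushwalk counted: 2 × (20/60) / 4.34 = 0.15 h/week (0.17 to 0.15 over the same windows).
- Indoor arm: 0. Baseline, both arms: 0.

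**What lowers it.** A man who answers about 10 days late has session 9 at 21 + 10 = 31 days, outside a 30-day window. One session remains: 1/4.34 = 0.23 h/week. Missed sessions, and walking sessions moved indoors in extreme weather (Walking safety protocol), also reduce it.

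**Consequence for p values.** The SD of change is an assumption, shown as a range. The table gives the probability of two-sided p<0.05 when contact outside therapy has not changed at all (two-sample noncentral t, 56 per arm, nominal 5%). It assumes that every walk-and-talk man carries the full shift.

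| Assumed SD (h/week) | d at 0.46 h/week | P(p<0.05) | d at 0.15 h/week | P(p<0.05) |
|---|---|---|---|---|
| 1 | 0.46 | 68% | 0.15 | 13% |
| 2 | 0.23 | 23% | 0.08 | 7% |
| 5 | 0.09 | 8% | 0.03 | 5% |
| 10 | 0.05 | 6% | 0.02 | 5% |

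The article reads d = 0.2 as small. At an SD of 2 h/week, the full-hour shift alone would be reported as a small effect.

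**The case against.** The strongest reply is that the article never claims change outside therapy. It speaks of impacts of the programme, and an hour's walk through a wetland reserve is one. The introduction to walk-and-talk therapy names nature exposure during sessions as a possible route to benefit, and the rationale for the primary outcome also cites nature exposure. For total exposure, counting the sessions is correct. This stands, and it is why the item should be kept as collected.

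The size is also open to challenge. The 0.46 h/week assumes full outdoor attendance, prompt survey completion, and men who count the whole hour. The item asks what the man himself considers contact with nature, and part of the route is paved and near buildings. The high false-positive figures need an SD near 1 h/week, which nothing in the article supports over a larger one. Men who answer only the abbreviated DASS-21 survey give no reading, so 56 per arm may be too many. All of this stands: the figures are upper bounds under stated assumptions.

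A reader might go further and infer that no time point is free of session exposure, or that the planned mediation analyses are contaminated. The documents do not support either. Baseline precedes all sessions, and late responders may have little or no overlap. The Discussion mentions mediation but does not name nature contact as a mediator; if exposure during sessions is the proposed pathway, removing it would remove the mechanism under test.

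The reply does not remove the ambiguity of the behavioural label, or the one-sided direction of the overlap.

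**Conclusion.** The concern holds as a limit on interpretation. For men on schedule, the 5-month score in the walk-and-talk arm can contain up to about 0.46 h/week of delivered therapy (0.15 h/week if only the bushwalk is counted), with no counterpart in the indoor arm or at baseline. No post-baseline reading is designed to be free of it. A group-by-time difference on this item therefore cannot, by itself, show that men changed their contact with nature outside therapy.

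The size rests on a month of about 30 days, the stated session and survey timing, full outdoor attendance, and men counting session time. The effect on p values depends on an SD that the article does not give: near nominal at 5 h/week or more, substantial near 1 h/week.

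It would be too strong to call the outcome invalid or its estimate biased in general. It is biased only as a measure of contact outside therapy; as total contact it is sound. The outcome is exploratory, and the primary outcome and sample size are untouched, so this is a minor point.

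**What to change.** Keep the item as collected. Label the 5-month result 'total nature contact, including therapy sessions', and do not present it alone as a behavioural change.

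Add one sensitivity analysis. For each walk-and-talk man, take the sessions logged as attended and held in the intended setting (Attendance, fidelity and adherence) in the month before his survey date. Convert them to hours per week at 0, 20 and 60 minutes per session, subtract, and floor the result at zero. Rerun the group-by-time model at each value. Claim change outside therapy only if the finding holds across the whole range.

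The cost is a sentence of reporting text and one derived variable from session logs already collected. Post-intervention assessments are complete, so the 5-month item cannot be reworded, but the analysis can still be specified before results are examined.

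The downside is real. The logs record attendance and setting as yes or no, not outdoor minutes; routes could be shortened or part of a session spent on a bench; and some men may never have counted their sessions, in which case subtraction overcorrects against walk-and-talk. The adjusted values are bounds, not a replacement outcome.

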### Physical activity

Physical activity was measured using YAMAX SW200 pedometers. Participants were given a pedometer and log sheet to record their daily step count over 7 days. For the baseline measurement, participants were express mailed the pedometer and log sheet approximately 9 days prior to their first session (allowing 2 days for postage and 7 days for logging) and were asked to return them at their first session. Similarly, for the post-intervention measurement, participants were mailed the pedometer, log sheet and a paid reply package prior to their last session, and were asked to mail them once they have completed/recorded their step count over 7 days, or return it at their last session.

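### The post-intervention pedometer week is not anchored and can include the last session, so a 5-month step difference can partly be the therapy walk itself

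*Protocol article*

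**What the plan says.** All references are to the protocol article.

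- **Measure** (Physical activity): "Participants were given a pedometer and log sheet to record their daily step count over 7 days".
- **Baseline week** (same section): the device is posted about nine days ahead of the first session, two days for the post and seven for logging. Men "were asked to return them at their first session".
- **Post-intervention week** (same section): "for the post-intervention measurement, participants were mailed the pedometer, log sheet and a paid reply package prior to their last session". No lead time or start day is given. Men "were asked to mail them once they have completed/recorded their step count over 7 days, or return it at their last session".
- **Session content** (Interventions): the walk-and-talk session "occurred while walking along an approximately 4 km predetermined route on the University campus"; the indoor session is seated. Psychologists may vary the walk, for example by "extending or shortening the route, or sitting at an outdoor bench for part of the session". Sessions are fortnightly.

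Nothing in the article excludes the session day from the step log, asks men to take the pedometer off for the session, or has session steps recorded separately.

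**The concern.** The two pedometer weeks are not defined alike. The baseline week is tied to the days before any therapy. The later week is tied to nothing beyond a posting date some time before the last session, and a prepaid return lets recording continue through or past that session.

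If the session day falls inside the log, its content differs by arm because it is the treatment: a long walk in one arm, a chair in the other. The extra steps can then appear only at 5 months and only in the walk-and-talk arm. A group-by-time comparison would count that pattern as an intervention effect, and randomisation does not remove it. A reader could take the difference as a change in everyday activity when part of it is one walk that ends with the course of therapy.

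**Working it through.** **Figures in the plan.** The article gives no figure for steps. Its only calculation is for the DASS-21. With two-sided alpha assumed, 2 × (1.96 + 0.8416)² × 15² / 8² = 55.2, so 56 per group. Then 56 / 0.75 = 74.7, so 75 per group and 150 in all. This reproduces the Sample size section and is not involved in the point.

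**Inputs.**
- Route of about 4 km, one session per fortnight (Interventions).
- Log of 7 days (Physical activity).
- Step length 0.65 to 0.80 m: assumed; the article gives none.
- Share of walk-and-talk men whose log includes a walked last session: unknown; 25%, 50% and 75% shown.

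**1. Which logs contain the session.** Call the session day 0. A log starting on day s covers days s to s + 6, so it contains day 0 when s lies between −6 and 0, which is seven possible start days. Starting on day −7 or earlier, or day 1 or later, avoids it. The baseline schedule gives s = −9 + 2 = −7 and ends on day −1, just clear of the session. The post-intervention text gives no such s.

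**2. Steps in one walk.** Distance / step length: 4,000 / 0.80 = 5,000 and 4,000 / 0.65 = 6,154.

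**3. Effect on an affected man's 7-day mean.** 5,000 / 7 = 714 and 6,154 / 7 = 879, that is about 715 to 880 steps/day. The indoor session adds 0.

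**4. Against the true average during treatment.** One walk per 14 days is 5,000 / 14 = 357 to 6,154 / 14 = 440 steps/day. A log with the session therefore counts the walk at twice its average rate, and a log without it counts zero.

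**5. Arm-level shift = share × step 3.**

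| Share affected | Shift (steps/day) |
|---|---|
| 25% | 179 to 220 |
| 50% | 357 to 440 |
| 75% | 536 to 659 |

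**6. Sensitivity.** For an assumed route of 3 to 5 km, reflecting the permitted variation, step 3 becomes 3,000 / 0.80 / 7 = 536 to 5,000 / 0.65 / 7 = 1,099. If only 80% of the included sessions were actually walked (assumed), the 50% row falls to 0.8 × 357 = 286 to 0.8 × 440 = 352. All figures are gross: ordinary steps displaced during that hour would lower them. The article gives no standard deviation for steps, so no standardised size can be derived from it.

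**The case against.** **This is analysis-plan detail.** Which logged days enter a step mean is often left to the statistical analysis plan, which is not shown. That stands for the summary rule, and if that plan already drops session days the point is met. The recording window, however, is set in the article, and it is set differently at the two time points.

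**The later week mirrors the baseline week.** The text introduces it as similar, and a man who hands the device in at the last session has most naturally stopped logging before the walk. This stands: inclusion is permitted, not required. A reader might infer that every post-intervention log contains the therapy walk; the article does not support that. Clear exposure needs the mail-back route and a start day in the seven identified above.

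**Therapy steps are real activity.** The article's rationale includes the benefit of walking, so total activity is a legitimate target. This stands too, but it does not rescue the comparison. With fortnightly sessions, a 7-day log gives the walk either double weight or none, depending on when each man began.

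**The affected analysis is inferred.** Table 1 lists the IPAQ, not pedometer steps, as the physical-activity outcome. The Discussion names physical activity and mediation only in general terms. It is tempting to say that a planned mediation analysis is contaminated, but no passage names steps as a mediator. The IPAQ asks about the last 7 days in a survey completed about a week after the last session (Measures), so its recall falls largely after the final walk.

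**The size rests on assumptions.** Agreed. Shortened or partly seated routes and sessions moved indoors in extreme weather (Walking safety protocol) also reduce it.

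**Conclusion.** The point holds as a minor one. The post-intervention pedometer window is loose enough to include the last session, whose step content differs by arm by design, and the baseline window is not. For each walk-and-talk man whose log includes a walked 4 km session, the 7-day mean rises by up to about 715 to 880 steps/day, gross, at a step length of 0.80 to 0.65 m. The arm-level shift is about 180 to 660 steps/day if 25% to 75% of men are affected. That share cannot be learned from the article and could be lower.

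It would go too far to conclude that any step difference is an artefact, or that the trial's main result is at risk. Men who finish logging before the session or start after it contribute none of this shift. The DASS-21 primary outcome, the sample size and the IPAQ outcome in Table 1 are not materially touched. What is at stake is how a 5-month pedometer difference may be read.

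**What to change.** Post-intervention assessments are complete (Study design), so the window cannot be re-set, but the analysis rule can be.

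- **Where log dates and session dates can be matched:** compute mean daily steps over non-session days, identically in both arms and at both time points, as the measure of activity outside therapy. Report the all-days mean beside it, labelled as including the therapy walk.
- **Where days cannot be dated:** report the limitation and do not interpret a step gain as changed habitual activity.

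Counts were logged daily, sessions had a recurring fortnightly slot, and psychologists logged each attended session and whether it took place in the intended setting (Attendance, fidelity and adherence). The article does not say whether the step log sheets carry calendar dates, and this should be checked first. The cost is a sentence or two in the analysis plan, the date matching, and at most one logged day lost per man at each time point.
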